#### General Psychological Distress

We will measure general psychological distress on the DQ5 [45]. The DQ5 comprises 5 items that ask the respondents to indicate the frequency with which they have experienced a range of distressing situations, thoughts, and feelings over the previous 30 days. The scale assesses these statements on a 5-point Likert scale ranging from 1=*never* to 5=*always*. Items include “My worries overwhelmed me,” “I felt hopeless,” and “I found social situations upsetting.” Scores are summed to produce a total score (range 5-25), with higher scores indicating more severe levels of psychological distress. The DQ5 has demonstrated high internal consistency (Cronbach α=0.86) and validity in previous studies [45,55].

#### Quality of Life

To measure the impact of the program on quality of life and for the economic evaluation, we will use the ReQoL-10 Questionnaire [46], which is a validated measure and highly suitable for measuring recovery and quality of life in the mental health context. The ReQoL-10 comprises 11 items, including 10 focused on mental health and 1 focused on physical health. The mental health items assess the frequency experienced over the last week of the thoughts, feelings, or activities mentioned, such as “I could do the things I wanted to do” and “I felt lonely,” assessed on a scale from 0=none of the time to 4=most or all of the time. Negatively worded items are reverse scored. The 11th item assesses the severity of physical health problems, including “problems with pain, mobility, difficulties caring for yourself or feeling physically unwell” experienced on a 5-point scale from 4=no problems to 0=very severe problems. The scale has been validated, with Cronbach α ranging from 0.87 to 0.92 [46,56], and has been used in economic evaluations of mental health interventions [57]. A UK-derived value set will be used to calculate utility values at each time point. The area under the curve method will be used to calculate QALYs from utility values.

#### Work and Activity Functioning

The WPAI questionnaire will be used to measure the effect of health problems on the ability of the participants to work and perform daily activities, and it will also be used for economic evaluation purposes. We altered the original WPAI questionnaire to assess days (as opposed to hours) during the past month (30 days). The original WPAI questionnaire comprises 6 questions; we will omit the first question which asks if the respondent is employed given our target group, retaining the 5 questions targeting (Question 1, Q1) the number of days missed due to health problems, (Q2) the number of days missed for other reasons, (Q3) the number of days worked, and (Q4) degree health problems affected productivity while working on 0 to 10 Visual Analogue Scale (VAS); (Q5) degree that health problems affected productivity in regular unpaid activities on 0 to 10 VAS [47]. We will derive percentage scores for absenteeism, presenteeism, work productivity loss, and activity impairment based on the predefined scoring methods [58]. Previous studies have provided support for the validity of the original scale [59].

#### Implementation Measures: Acceptability, Appropriateness, and Feasibility

To provide information regarding implementation outcomes, we will use the 3 measures designed by Weiner et al [60] that assess the acceptability, appropriateness, and feasibility of the intervention. Each of the 3 scales has 4 items assessing the acceptability (eg, “the intervention is appealing to me”), the appropriateness (eg, “the intervention seems suitable”), or the feasibility (eg, “the intervention seems easy to use”) of the program. The items are responded to on a scale ranging from 1 to 5, where 1=completely disagree and 5=strongly agree. Total scores on each scale can range from 4 to 20, with lower scores indicating a lack of each construct (acceptability, appropriateness, and feasibility). The scales demonstrate good validity, and the internal consistency is high for the 4-item scales, with Cronbach α ranging from 0.85 to 0.91 [60]. In addition, we will examine adherence levels (intervention completion), attrition, and factors associated with these indicators of engagement. Follow-up interviews (described in the Quality Assurance and Monitoring section) will also be used to inform the future implementation of the intervention in workplaces.

### Power and Recruitment

Our study’s power and sample size estimations were informed by the primary outcome measure: the level of intention to seek help from professional sources, as measured by the GHSQ. Using data from the MATES in Construction workplace trial [61], a conservative intraclass correlation of 0.02 was assumed to estimate the design effect. An RCT [62] exploring the potential effectiveness of a web-based program designed to increase help-seeking intentions for social anxiety disorder informed the anticipated difference between pre- and posttest GHSQ scores (standardized mean difference=0.2). Because the size of the workplace clusters could not be anticipated ahead of time, a conservative average cluster size ranging from 25 to 35 was assumed. We assumed 15% attrition in participant numbers from pre- to postintervention, a conservative assumption based on previous workplace trials [63] and accounting for the single-session nature of the intervention. To detect an effect size of Cohen *d*=0.2 between the intervention and comparison arms with 80% power, using a 2-tailed type I error level of 0.05, we need to recruit between 30 and 36 workplaces (assuming each workplace has 25 to 35 participants), resulting in a minimum of 900 employees.

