### Recruitment Procedures and Randomization

#### Workplace Recruitment

Recruitment of workplaces is expected to be conducted using our existing networks through the The Mental Health Australia General Clinical Trials Network. We plan to recruit approximately 30 to 36 workplaces, with 25 to 35 participants per workplace to meet our total sample size target of 900 adult participants. Workplaces will be eligible if they (1) report having at least 50 employees to ensure that each cluster is viable and (2) have an Employee Assistance Program (EAP) available for their staff to ensure that employees experiencing mental health concerns can access effective and immediate care. Any industry of work is eligible for inclusion. A mixture of general and high-risk workplaces (ie, those likely to be exposed to situations that may impact mental health, such as health care settings) initially in the Australian Capital Territory, New South Wales, and Victoria are being targeted. Recruitment is highly feasible based on previous public health trials conducted by the team (N=849 to 2773 [34-36]), and our universal cluster-based trials have typically recruited high numbers (eg, N=1477 [37] and N=1633 [38]).

We will invite workplaces through multiple channels, including directly via an email invitation addressed to the “key representatives” from a workplace such as managers or staff in charge of human resources, via telephone calls, and via invitation emails to employees in our existing networks. We will contact the workplace key representatives who express interest to determine organization characteristics and eligibility for the study.

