#### Randomization

Given the cluster design, we will use a minimization approach to randomization [39]. Minimization is a type of randomization where the first participant (or cluster) is randomized and subsequent selections are allocated in a way that minimizes the imbalance on specific factors between groups. This method is helpful for a design with few participants (or clusters) and has the advantage of making each condition more closely matched on key factors across the trial. To implement this, we will use a preprogrammed computer algorithm that will assign each new workplace recruited into the trial into a condition. This process will aim to balance across conditions on the following key workplace characteristics: (1) workplace type (office-based vs non–office based), (2) organization size (<200 vs >200 employees), and (3) location (Australian Capital Territory or New South Wales or Victoria vs other Australian state or territory). Once a workplace has been allocated a condition, we will discuss with their key representative what participation in the trial involves and provide them with an email or SMS text message (depending on their preferred communication with employees) with an embedded link to their assigned study recruitment website. We expect the text to read as follows:

Would you like to participate in a research study testing a new resource for supporting employee wellbeing? Learn more about your mental health and wellbeing by completing a survey and a brief online program today: <link>.

We will ask the workplaces to send invitations to all their employees themselves, with each workplace determining who from within their organization will send this invitation. This process is designed to increase ecological validity, as the goal for the program is for it to be delivered by workplaces, we expect this to be a minimal burden (ie, 1 or 2 SMS text messages or emails) on the workplace administration staff tasked with sending invitations.

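### The power calculation uses only an average cluster size; if recruitment ends near 900 people, the unequal workplaces the design will produce lower the power further below the stated 80%

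*Protocol article*

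**What the plan says.** All references are to the protocol article. The Power and Recruitment section sets its target "To detect an effect size of Cohen *d*=0.2 between the intervention and comparison arms with 80% power", tested two-sided at the 5% level and allowing for 15% loss between pretest and posttest. On clustering it says that "a conservative intraclass correlation of 0.02 was assumed to estimate the design effect". On size it says that "a conservative average cluster size ranging from 25 to 35 was assumed", and the reason it gives is that sizes were not known in advance. The result is 30 to 36 workplaces, on the premise that each supplies 25 to 35 people, and a minimum of 900 employees.

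Two other sections govern how large the clusters will be. Under Workplace Recruitment, an employer is eligible if it can "report having at least 50 employees to ensure that each cluster is viable"; no upper limit is given. Under Randomization, one of the minimization factors is "organization size (<200 vs >200 employees", so employers on both sides of 200 are expected, and "We will ask the workplaces to send invitations to all their employees themselves". The figure of 25 to 35 per workplace is a planning target. No cap or stopping rule per workplace is stated.

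**The concern.** The premise of 25 to 35 participants at every site amounts to nearly equal clusters. The recruitment procedure does not produce that. Twenty-five participants is 50% uptake at a 50-person employer but about 6% at a 400-person employer (25/400), so near-equal clusters would need uptake to fall in proportion to employer size.

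For a given total and mean size, unequal clusters carry less information than equal ones, because extra people in a large cluster add little. Planning on the mean alone then overstates power. The article also names 900 people as the sample size target and gives the number of workplaces as approximate, so recruitment could be judged complete on headcount. At stake is whether the primary comparison of help-seeking intentions has the sensitivity claimed for it.

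**Working it through.** **Inputs from the Power and Recruitment section.** d = 0.2 (SD 1), two-sided α = 0.05, power 80%, ICC 0.02, attrition 15%, average cluster size 25 to 35, 30 to 36 workplaces, at least 900 recruited. **Assumptions:** 1:1 allocation, and a CV of cluster size of 0.4 to 1.0. The article gives neither.

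**Step 1: the plan's own figure.** Without clustering, n per arm = 2 × (1.960 + 0.842)² / 0.2² = 393, or 786 in total. The design effect for equal clusters is DE = 1 + (m − 1) × 0.02, and the number to recruit is 786 × DE / 0.85.

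- 25 recruited per site, so m = 0.85 × 25 = 21.25 analysed: DE = 1.405, recruit 1,300, or 52 workplaces.
- 35 recruited per site, so m = 29.75 analysed: DE = 1.575, recruit 1,457, or 42 workplaces.
- Applying DE to the recruited size instead gives 1,369 (55 workplaces) and 1,554 (45 workplaces).

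The stated 30 to 36 workplaces and 900 people are therefore not reproduced from the stated inputs. They are approached if an unstated pre-post correlation r of about 0.58 is brought in: 786 × (1 − 0.58²) × 1.48 / 0.85 = 908 at 25 per site (36.3 workplaces), and the same formula with DE 1.68 gives 29.5 workplaces at 35 per site. Whether this was done cannot be told from the article.

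**Step 2: allow for unequal sizes at a fixed total of 900.** Analysed N = 0.85 × 900 = 765. With m the mean analysed size, DE = 1 + ((1 + CV²)m − 1) × 0.02. The effective sample size is 765 / DE, and power = Φ(0.2 × √(N_eff/4) − 1.960). For 36 × 25 at CV 0.6: DE = 1 + (1.36 × 21.25 − 1) × 0.02 = 1.558; N_eff = 491; power = Φ(2.216 − 1.960) = 60.1%. With r = 0.6 the SD becomes √(1 − 0.36) = 0.8.

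| CV | 36 × 25, no r | 30 × 30, no r | 36 × 25, r = 0.6 | 30 × 30, r = 0.6 |
|---|---|---|---|---|
| 0 | 64.6% | 62.0% | 83.1% | 80.9% |
| 0.4 | 62.5% | 59.7% | 81.3% | 78.8% |
| 0.6 | 60.1% | 57.1% | 79.1% | 76.2% |
| 1.0 | 53.4% | 49.8% | 72.4% | 68.6% |

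**Step 3: how the formula's pessimism matters.** An analysis that weights clusters efficiently loses less. For 30 × 30 without baseline adjustment, simulated cluster sizes give 60.6%, 58.9% and 54.5% at CV 0.4, 0.6 and 1.0, against 62.0% with equal clusters.

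**Step 4: what CV is plausible.** If sites really stayed within 25 to 35, spread evenly, the CV would be about 0.10 and the loss about 0.1 point. Equal numbers of 100- and 400-employee sites at equal uptake give mean 250, SD 150 and CV 0.6. At 12% uptake that mix yields 12 and 48 participants, a mean of 30. This mix is illustrative.

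**Step 5: let the total grow instead.** Keep the workplaces and let large sites add people, at CV 0.6 and with no baseline adjustment. Thirty sites averaging 60 give 72%, and 36 give 80%. Thirty averaging 125 give 82%, and 36 give 88%.

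**The case against.** The strongest reply is that the absence of a cap does not itself cost power. The article says 30 to 36 workplaces are needed and calls 900 a minimum. If those workplaces are recruited and large ones overfill, total N rises and, as Step 5 shows at CV 0.6, so does power compared with the planned 900 in equal clusters. This stands. A reader might infer that inviting all employees without a cap lowers power, but the article does not support that. The loss applies only if recruitment ends near 900 or the mean stays at 25 to 35.

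Second, calling the average conservative can be defended: with the number of workplaces fixed, a small assumed yield per site is the cautious choice. This also stands. The word misleads only when the total is fixed, because a small mean then reduces the design effect.

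Third, the size of the loss rests on a CV that the article does not give, and at moderate values it is small beside the shortfall already present with equal clusters. Both are true. A floor of 0.6 for the CV cannot be drawn from the documents.

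Fourth, one might picture 900 people coming from 15 sites of 60, where power is about 50%. That is half the stated minimum number of workplaces, and the article says that site recruitment and participant numbers will be monitored closely. It shows why the number of sites should bind, not what the plan intends.

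Fifth, a condensed article may leave design-effect detail to the full protocol. But the article does state the cluster-size premise, its characterisation and the resulting power, and those statements can be checked against its own recruitment rules.

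**Conclusion.** The concern holds for a total fixed near 900. The stated power rests on an average cluster size alone, while the eligibility and invitation rules will produce clusters of differing size. On the stated inputs, power is about 62–65% with equal clusters. Variation in size then takes off about 2 points at CV 0.4, 4 to 5 at CV 0.6 and 11 to 12 at CV 1.0 (about 7 to 8 at CV 1.0 with efficient weighting). The gap of about 15 to 18 points between the stated 80% and the equal-cluster figure is the larger problem and has a separate cause.

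The point does not depend on that gap. If a pre-post correlation of about 0.6 lies behind the stated figure, equal clusters give 81–83%, and CV 0.6 brings this to 76–79%. These results assume 1:1 allocation, the normal approximation and the stated ICC; the CV range is an assumption throughout.

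**What to change.** 1. Recompute the design effect as 1 + ((1 + CV²)m − 1) × ICC over a stated range of CV, for example 0.4 to 1.0.
2. State any pre-post correlation used in the sample size, and restate the power accordingly.
3. Qualify the word conservative as applying only with the number of workplaces held fixed.
4. Make the number of workplaces, already given as 30 to 36, a binding recruitment criterion alongside the 900, so that reaching 900 people from fewer sites does not end recruitment.

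Items 1 to 3 cost a recalculation and a few sentences, and the reported power will be less favourable. Item 4 confirms a number the article already states and needs no cap on large sites. Restating the power does not restore it. Reaching 80% from the stated inputs without baseline adjustment at CV 0.6 would take about 1,441 people in 58 workplaces (25 per site) to 1,655 in 48 (35 per site), against about 1,300 to 1,457 with equal clusters.

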**Methods:**

A 2-arm cluster randomized controlled trial will be conducted (target sample: N=900 from 30 to 36 workplaces, with n=25 to 35 participants per workplace). The trial will compare the relative effectiveness of an enhanced interactive program (intervention condition) with a standard psychoeducation-alone program (active control condition) on the primary outcome of professional help-seeking intentions as measured by the General Help-Seeking Questionnaire. Secondary outcomes include the impact on mental illness stigma; mental health literacy; help-seeking attitudes and behavior; work and activity functioning; quality of life; and symptoms of mental ill-health including depression, anxiety, and general psychological distress.

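### The 80% power claimed for d = 0.2 with 900 participants does not follow from the printed inputs, which give about 62–65%

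*Protocol article*

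**What the plan says.** The Power and Recruitment section of the protocol article gives a full set of inputs and a result.

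- Target: "To detect an effect size of Cohen *d*=0.2 between the intervention and comparison arms with 80% power". The test is two-sided at the 5% level.
- Clustering: "a conservative intraclass correlation of 0.02 was assumed to estimate the design effect", with an average of 25–35 participants per workplace.
- Attrition: "We assumed 15% attrition in participant numbers from pre- to postintervention".
- Result: "we need to recruit between 30 and 36 workplaces (assuming each workplace has 25 to 35 participants), resulting in a minimum of 900 employees".

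The Abstract repeats the target as "target sample: N=900 from 30 to 36 workplaces, with n=25 to 35 participants per workplace", and Workplace Recruitment ties the same ranges to a total of 900. No correlation between pretest and posttest scores on the General Help-Seeking Questionnaire (GHSQ) is stated, and no variance reduction from baseline is claimed.

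**The concern.** A between-arm effect of 0.2 SD is small. An individually randomised comparison at 80% power already needs nearly 800 analysed participants. A cluster trial with workplaces of 25–35 and an intraclass correlation of 0.02 needs roughly 40–60% more, and 15% attrition comes on top. A total of 900 looks too small to contain all three.

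This paragraph is the only justification given for the sample size of the primary hypothesis. Limitations and Risks treats loss of power as a matter of recruiting too few people. A reader is therefore led to believe that reaching 900 secures 80% power for d = 0.2. If the printed inputs do not support that, the reader cannot tell what effect the trial is able to detect.

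**Working it through.** **Inputs.** All are from Power and Recruitment: d = 0.2 (SD = 1), two-sided α = 0.05, power 80%, ICC = 0.02, m = 25–35 per workplace, 15% attrition. Two assumptions are added because the article gives no figure: 1:1 allocation and equal workplace sizes. Unequal sizes would lower power further.

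**1. Can the stated figure be reproduced?** Without clustering, total analysed = 4 × (1.96 + 0.8416)² / 0.2² = 785. Allowing for attrition, 785 / 0.85 = 924 recruited, which already exceeds 900. This is the nearest match found: 900 recruited leaves 765 analysed, and with no design effect that gives 79.0% power. It is only an inference that clustering was left out, because the article does not show its formula and says that a design effect was estimated.

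**2. Sample size with the design effect.** DE = 1 + (m − 1) × 0.02, and recruited N = 785 × DE / 0.85. DE can be based on the retained workplace size (0.85m) or the recruited size (m).

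| m | DE, retained size | Recruited N (workplaces) | DE, recruited size | Recruited N (workplaces) |
|---|---|---|---|---|
| 25 | 1.405 | 1,298 (52) | 1.48 | 1,367 (55) |
| 30 | 1.490 | 1,377 (46) | 1.58 | 1,460 (49) |
| 35 | 1.575 | 1,455 (42) | 1.68 | 1,552 (45) |

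The article states 900 in 30–36 workplaces.

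**3. Power of the stated designs.** Effective n = 0.85N / DE, using the more favourable retained-size DE. Power = Φ(0.2 × √(effective n / 4) − 1.96).

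- 36 × 25 = 900: 765 / 1.405 = 544, so Φ(2.333 − 1.96) = 64.6%.
- 30 × 30 = 900: 765 / 1.490 = 513, so Φ(2.266 − 1.96) = 62.0%.
- 36 × 35 = 1,260, the largest stated design: 1,071 / 1.575 = 680, so Φ(2.608 − 1.96) = 74.1%.

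A t-test on workplaces minus 2 degrees of freedom gives 62.1%, 59.0% and 71.7% respectively.

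**4. Does another convention explain 80%?** At 900, ignoring attrition gives 69.4% (36 × 25) or 66.5% (30 × 30). A one-sided test gives 75.4% or 73.3%. Even 36 × 35 with attrition ignored gives 78.2%.

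**5. Effect detectable at 900 with 80% power.** d = 2.8016 × √(4 / effective n), which is 0.240 for 36 × 25 and 0.247 for 30 × 30.

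**6. Correlation that would restore 80% at 900.** The variance must shrink to 544 / 785 = 0.694 (36 × 25) or 513 / 785 = 0.654 (30 × 30) of its posttest value.

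- Baseline adjustment, factor 1 − r²: r = √(1 − 0.694) = 0.55, or √(1 − 0.654) = 0.59.
- Change contrast, factor 2(1 − r): r = 1 − 0.694/2 = 0.65, or 1 − 0.654/2 = 0.67.

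Power at 900 over a range of assumed r (36 × 25 / 30 × 30):

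| r | Baseline-adjusted | Change contrast |
|---|---|---|
| 0.3 | 69% / 66% | 51% / 48% |
| 0.5 | 77% / 74% | 65% / 62% |
| 0.6 | 83% / 81% | 74% / 72% |
| 0.7 | 90% / 89% | 85% / 83% |

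Step 6 assumes that d is scaled to the posttest SD and that r is the same at individual and workplace level.

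**The case against.** The strongest reply is that 62–65% is the power of a comparison that gains nothing from baseline, and that is not the planned analysis. The Estimand section defines the effect by change from before to after the program. Data Analysis plans a repeated-measures mixed model, and Table 1 collects the GHSQ at pretest. Trial Delivery expects both surveys to be completed mostly in one sitting, so a high correlation is possible. A condensed article may also leave the assumed correlation to the full protocol.

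Much of this stands. A reader might infer that the trial as planned has about a one-in-three chance of missing d = 0.2. The documents do not support that, because power under the planned analysis depends on a correlation that they do not give. The reply does not rescue the printed statement, though. The article lists its inputs and presents 900 as their result, with no mention of a gain from baseline. With a low correlation, a change contrast would do worse than 62–65%, not better.

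Three further criticisms may tempt a reader, and none is supported.

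- *Calling the cluster size conservative is wrong.* It is defensible. With the number of workplaces fixed, smaller workplaces mean less power (30 × 30 gives 62.0%, 30 × 35 gives 66.3%).
- *The ranges allow 30 × 25 = 750.* Workplace Recruitment ties the ranges to the 900 target, so they read as inverse pairs such as 36 × 25 and 30 × 30.
- *The 0.2 is a within-arm change.* It is introduced as "the anticipated difference between pre- and posttest GHSQ scores (standardized mean difference=0.2", but it comes from a randomised trial and could be a between-arm difference in change. That cannot be settled without the cited trial, and the article then says plainly that 0.2 is the between-arm target.

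**Conclusion.** The sample size statement is wrong as printed. Its inputs need about 1,300–1,550 recruited for 80% power at d = 0.2. At 900 they give about 62–65%, or about 59–62% with a t-test on workplace degrees of freedom. No combination within the stated ranges reaches 80%.

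The conclusion is limited to the printed inputs. It rests on 1:1 allocation, equal workplace sizes and no gain from baseline. It does not establish that the planned analysis is underpowered.

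**What to change.** Correct the paragraph in one of two ways.

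- Report that 900 recruited gives about 62–65% power for d = 0.2, and 80% power for d of about 0.24–0.25.
- Or state the assumed pre-post GHSQ correlation with its source, name the baseline-adjusted primary model that uses it, and recompute with the ICC of 0.02 and the 15% attrition both included.

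The cost is a few sentences and one recalculation. No participants or workplaces need to be added. The stated power becomes less favourable unless a sufficient correlation can be justified.
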